### DNA methylation

At baseline (visit 2) and end of study (visit 4), all participants will provide a sample of whole blood to conduct DNA methylation testing with TruDiagnostic™, based in the United States of America (USA). Samples may be taken separately by finger-prick lancet onto the provided blood spot card, or whole blood can be taken from a no-additive sample tube already taken from the participant by venipuncture at the time. Preparation of the blood spot card will be according to the instructions provided by TruDiagnostic™. Collected samples will be stored at the site, at room temperature, and sent in batches to the TruDiagnostic™, no less than every 8 weeks to ensure that samples are viable when arriving at the analysis laboratory in the USA. Samples will be destroyed following analysis. Individual results will not be provided to participants as samples will be deidentified. If blood samples are lost or damaged and cannot be shipped for analysis, participants will be asked to provide another sample if the sample was lost within a week of providing the initial sample.

### SF36 questionnaire

Participants will be asked to complete theSF36 QoL questionnaire at baseline (visit 2) and end of study (visit 4). The questionnaire should be completed when the participant arrives at the study site for their appointment prior to any other activity occurring. The participant will be provided with the questionnaire on a tablet by the study staff and should complete the questionnaire unaided to ensure accurate answers from the participant.

### Participant diary

At baseline (visit 2) and visit 3, participants will be provided with a printed diary to complete daily. Information to be recorded will be the date, study required exercise program completed or any deviation from the assigned exercise program, other exercise completed that day not required by the protocol, study medication administration, and recording of any adverse event that has prevented the participant from completing the assigned exercise program or the assigned rapamycin dosing schedule.

### Data quality assurance

To promote data quality, assessors will receive training on standardized procedures for each outcome measure. Duplicate measurements will be taken when necessary to ensure accuracy. Data collection forms will be available in the protocol appendix for reference.

## Plans to promote participant retention and complete follow-up {18b}

To ensure high participant retention and complete follow-up, several strategies will be implemented throughout the study:Regular communication◦ Weekly contact will be maintained with all participants through phone calls, texts, or emails to discuss compliance with the exercise and medication regimen, address any concerns, and document adverse events. Each contact attempt will be documented in the participant’s source documents.Convenience and support◦ Exercycles will be delivered and installed at participants’ homes by Rutherford Fitness, ensuring they have the necessary equipment to complete the exercise program.◦ Participants will receive detailed instructions and support for using the exercycle and completing the exercise regimen.Monitoring and feedback◦ Participants will be monitored regularly for adherence to the study protocol. Weekly phone calls will include discussions about compliance, and any issues will be addressed promptly.◦ Participants will be encouraged to complete their daily diaries to record exercise activities, medication administration, and any adverse events. Compliance will be reviewed during the interim visit, and retraining will be provided as necessary.Adverse event management◦ Adverse events will be closely monitored and managed by blinded staff to ensure that participants’ safety is prioritized without compromising the blinding of the study.◦ Participants experiencing significant adverse events will be consulted with the principal investigator to determine the best course of action, including the possibility of unblinding if necessary for safety reasons.Data collection for withdrawn participants◦ Efforts will be made to collect outcome data for participants who discontinue or deviate from the intervention protocols. This includes attempting to conduct end-of-treatment (EOT) assessments for those who withdraw early from the study.◦ Participants who withdraw will be asked to return all study materials, including exercycles and study medication, and complete final assessments if they agree.Participant engagement◦ Regular updates on the study’s progress and findings (where appropriate) will be shared with participants to keep them engaged and informed about the importance of their contribution.

By implementing these strategies, the study aims to maintain high retention rates and ensure complete and accurate follow-up data.

### Data management {19}

Participants will be assigned a unique identifier by the sponsor. Any participant records or datasets transferred to the sponsor will contain the identifier only; participant names or any information that could make the participant identifiable will not be transferred.

Participants must be informed that their personal study-related data will be used by the sponsor in accordance with local data protection laws. The level of disclosure must be explained to the participant, who will be required to give consent for their data to be used as described in the participant information sheet and informed consent form (PISCF).

Participants must be informed that their medical records may be examined by quality assurance auditors and other authorized personnel appointed by the sponsor and by inspectors from regulatory authorities.

Information technology systems used to collect, process, and store study-related data are secured by technical and organizational security measures designed to protect such data against accidental or unlawful loss, alteration, unauthorized disclosure, or access.

Study participants will be provided with the option of receiving a summary of the study results.

Data entry and quality assuranceParticipant data relating to the study will be recorded on electronic case report forms (eCRFs) unless transmitted to the sponsor or designee electronically (e.g., laboratory data). The investigator is responsible for verifying that data entries are accurate and correct by physically or electronically signing the CRF.Guidance on completion of CRFs will be provided in the Data Management Plan and eCRF Completion Guidelines.Double data entry will be employed to ensure data accuracy, and range checks for data values will be implemented to identify and correct any discrepancies.Data quality will be promoted through predefined quality tolerance limits (QTLs) in the data management plan to identify systematic issues that can impact participant safety and/or the reliability of study results. These predefined parameters will be monitored during the study, and important deviations from the QTLs and remedial actions taken will be summarized in the clinical study report.

Data security and storageThe sponsor or designee is responsible for data management of this study, including quality checking the data.The sponsor assumes accountability for actions delegated to other individuals, such as contract research organizations.Records and documents, including signed PISCFs, pertaining to the conduct of this study must be retained by the investigator for 10 years after study completion unless local regulations or institutional policies require a longer retention period. No records may be destroyed during the retention period without written approval from the sponsor. No records may be transferred to another location or party without written notification to the sponsor.Source documents provide evidence for the existence of the participant and substantiate the integrity of the data collected. Source documents must be filed at the investigator’s site and may not be distributed to the sponsor if there is any risk of identifying any particular participant.Data reported on the eCRF that are transcribed from source documents must be consistent with the source documents or discrepancies must be explained. All current medical records for participants must be available for review as part of study documentation. The investigator will describe documents comprising source documents before the study commences by documenting these on the source document location list. This list must be maintained throughout the study, along with the source documentation, to support the data that have been entered into the eCRF.The sponsor or designee will perform monitoring to confirm that the data entered into the eCRF by authorized site personnel are accurate, complete, and verifiable from source documents; that the safety and rights of participants are being protected; and that the study is being conducted in accordance with the currently approved protocol and any other study agreements, ICH GCP, and Medsafe Guideline on the Regulation of Therapeutic Products in New Zealand Part 11.

### Confidentiality {27}

All participant data will be treated with the utmost confidentiality. Personal information about potential and enrolled participants will be collected, shared, and maintained to protect confidentiality before, during, and after the trial.

Data collectionParticipants will be assigned a unique identifier by the sponsor. Any participant records or datasets transferred to the sponsor will contain the identifier only; participant names or any information that could make the participant identifiable will not be transferred.Personal information, including contact details, medical history, and study-related data, will be collected and stored in secure databases. These databases will be protected by technical and organizational security measures designed to prevent accidental or unlawful loss, alteration, unauthorized disclosure, or access.

Data sharingAccess to personal information will be restricted to authorized personnel only. This includes study investigators, clinical site staff, and sponsor representatives who require access to carry out their responsibilities.Participants must be informed that their personal study-related data will be used by the sponsor in accordance with local data protection laws. The level of disclosure must be explained to the participant, who will be required to give consent for their data to be used as described in the participant information sheet and informed consent form (PISCF).Participants must be informed that their medical records may be examined by quality assurance auditors and other authorized personnel appointed by the sponsor and by inspectors from regulatory authorities.

Data maintenanceInformation technology systems used to collect, process, and store study-related data will be secured by technical and organizational security measures designed to protect such data against accidental or unlawful loss, alteration, unauthorized disclosure, or access.All records and documents, including signed PISCFs, pertaining to the conduct of this study must be retained by the investigator for 10 years after study completion unless local regulations or institutional policies require a longer retention period. No records may be destroyed during the retention period without written approval from the sponsor. No records may be transferred to another location or party without written notification to the sponsor.Source documents must be filed at the investigator’s site and may not be distributed to the sponsor should there be any risk of identifying any particular participant. Data reported on the eCRF that are transcribed from source documents must be consistent with the source documents or the discrepancies must be explained.

Data protection complianceMeasures will be taken to protect personal information in accordance with the Health Information Privacy Code 2020 (New Zealand) and relevant international data protection regulations, including the General Data Protection Regulation (GDPR) where applicable.The sponsor or designee will ensure that all data protection and confidentiality policies are adhered to throughout the study.

By implementing these measures, the study aims to ensure the confidentiality and protection of participant data before, during, and after the trial.

### Plans for collection, laboratory evaluation, and storage of biological specimens for genetic or molecular analysis in this trial/future use {33}

Collection of biological specimensBiological specimens, including blood samples for hematology, biochemistry, and DNA methylation analysis, will be collected at specified time points throughout the study.◦ Hematology and biochemistry: non-fasting blood samples will be collected at screening (visit 1) and at the end of the study (visit 4) for laboratory testing. This will include a full blood count, eGFR, urea and electrolytes, liver function tests (LFTs), HbA1c, lipids, IGF-1, and hs-CRP.◦ DNA methylation: whole blood samples will be collected at baseline (visit 2) and at the end of the study (visit 4) for DNA methylation analysis. These samples can be collected via finger-prick lancet onto a blood spot card or by venipuncture into a no-additive sample tube.

Laboratory evaluationHematology and biochemistry: samples will be analyzed according to local laboratory requirements, including full blood count, eGFR, urea and electrolytes, liver function tests, HbA1c, lipids, IGF-1, and hs-CRP. Safety blood samples, including full blood count, LFTs, and lipids, will also be collected at the interim visit (visit 3). Samples will be destroyed following analysis.DNA methylation: DNA methylation analysis will be conducted by TruDiagnostic™, based in the United States of America. Individual results will not be provided to participants as samples will be deidentified.

Storage of biological specimensShort-term storage: Collected samples will be stored at the clinical site at room temperature. Blood spot cards and other specimens will be kept in a secure, temperature-controlled environment to maintain their integrity until they are shipped for analysis.Long-term Storage and Shipping: Samples for DNA methylation analysis will be sent in batches to TruDiagnostic™ no less than every 8 weeks to ensure viability upon arrival at the analysis laboratory. Samples will be de-identified before shipping to maintain participant confidentiality. After analysis, the samples will be destroyed, and individual results will not be provided to participants.

Future use of specimensAfter analysis in this trial, all biological specimens will be destroyed.

Data management and confidentialityAll biological specimens will be labeled with a unique participant identifier to ensure anonymity. Personal identifying information will be stored separately and securely, accessible only to authorized personnel.Data derived from the analysis of biological specimens will be stored in secure databases protected by technical and organizational security measures to prevent unauthorized access or disclosure.

### Statistical methods

#### Statistical methods for primary and secondary outcomes {20a}

As some of the feasibility issues are related to the efficacy analyses, they are described first. The efficacy analysis plan is intended to match the analysis plan of the full trial closely.

Efficacy analysisAnalysis sets◦ Intention-to-treat (ITT) analysis set: This set will be used for the primary analysis and will include all randomized participants in their originally assigned groups.◦ Per-protocol (PP) analysis set: this set will be used for sensitivity analyses and will include participants who complete at least 75% of the exercise sessions and take at least 75% of the protocol-stipulated doses of sirolimus (rapamycin) or placebo.General inferential analysis plan◦ Outcomes at 13 weeks will be analyzed using regression models, adjusting for baseline values of the outcomes. Generalized linear models (GLM) will be employed, selected during a blind review of the data without knowledge of group allocation.◦ Final analyses will utilize the selected GLMs, and parametric assumptions will be addressed using the wild bootstrap method to estimate standard errors [35, 36]. For larger trials, standard sandwich estimators of the variance would be used in lieu of the bootstrap.Handling missing data◦ Multiple imputations will be used to create 15 completed datasets. The nominal significance level for this phase 2a study will be set at 0.1; however, in line with current thinking regarding preliminary studies, the results will deemphasize testing and emphasize point and interval estimation, producing confidence intervals for active arm effect having between 75% and 95% confidence levels in increments of 5 percentage points [27].Sensitivity analyses◦ Sensitivity analyses will be performed on the per-protocol analysis set and the complete-data-only set, excluding cases with missing data.

Safety analysisSafety analysis set: this set includes all randomized participants. Adverse events will be allocated on an as-treated basis:◦ Events occurring before cessation of treatment or completion of the trial will be assigned to the randomized arm.◦ Events occurring after cessation will be assigned to the placebo arm.Analysis of adverse events:◦ Counts of adverse events will be regressed on the allocation arm as described above in interaction with the graded severity using negative binomial regression.◦ Dichotomized relatedness to the intervention (classified as possible, probable, or definite) will be regressed on the allocation arm using a quasi-binomial framework with logarithmic link (relative risk regression) or a relative risk working model (e.g., Poisson with bootstrap estimation of the variance) to test for non-inferiority of the rapamycin arm. Standard errors will be estimated using the bootstrap, resampling participants. The modalities of non-inferiority will be detailed in the final analysis plan.

Feasibility analysesScreening and randomization rates: overall and weekly screening and randomization rates will be reported with Poisson-based 95% confidence intervals.Cessation and withdrawal rates: rates of drug treatment cessation, exercise program cessation, and study withdrawal will be reported and compared across randomization arms using a log-rank test.Residual variance estimation: the residual variance of each outcome will be estimated to inform the sample size and analytical design of the phase 3 trial.

Adherence to medicationAdherence reporting: adherence to the medication will be reported by arm at 6 and 13 weeks using mean percentage of supply used and compared between arms using binomial regression with bootstrap-based standard errors and *p*-values [30].Causal effect estimation: the causal effect of the medication on the primary outcome will be estimated using two-stage residual inclusion estimation, with the randomized allocation as the instrumental variable [31].

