## Participant timeline {13}

### Schedule of assessments

**Table Tabe:** 

Procedures and assessments	Visit 1	Visit 2	Visit 2a	Visit 3	Visit 4
	Screening	Baseline	Phone call	Interim assessment	EOS
	Day -28 to -1	Day 0	Within 6 days of baseline	Day 42±7	Day 91 +7
Informed consent	x				
Review of subject eligibility	x	x			
Demographics^1^	x				
Medical history	x				
Auscultate the heart to check for murmurs	x				
Vital signs^2^	x	x		x	x
ECG	x				
Hematology and biochemistry	x^3^			x^4^	x^3^
DNA methylation (TruDiagnostics)		x			x
SF-36 questionnaire		x			x
Assessment of ability to complete 30-Second Chair-Stand Test	x				
Randomization		x			
Allocation of weekly medication^5^		x		x	
Confirm participant day 1			x		
Weekly participant contact			x^6^		
Adverse event collection		x	x	x	x
Distribute subject diary card		x		x	
Collect subject diary cards				x	x
30-Second Chair-Stand Test		x		x	x
Hand grip strength		x		x	x
6-min walk test		x			x

^1^Race, gender at birth, contact details, height, and weight

^2^Resting heart rate, blood pressure, and oxygen saturation

^3^Full blood count, eGFR, urea and electrolytes, LFTs, HbA1c, lipids, IGF-1, hs-CRP

^4^Full blood count, LFTs, lipids

^5^Allocation of investigational product for 6-week period, followed by a 7-week period

^6^Participants are to be contacted by phone each week. Participants who cannot be reached following two phone contact attempts in a week can be sent a text message or email

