### Participant activities schedule

Weeks 1–13 exercise and dosing schedule.

Day 1 Week 1 must begin within 6 days of Day 0 (baseline visit).

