**Table Tabf:** 

**Weekly schedule**	**Exercise schedule**	**Dosing schedule**
Day 1	Training program	No treatment
Day 2	Rest day	No treatment
Day 3	Training program	No treatment
Day 4	Rest	No treatment
Day 5	Training program	No treatment
Day 6	Rest day	Placebo/rapamycin in the morning
Day 7	Rest day	No treatment

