### Adverse event reporting and harms {22}

Plans for collecting adverse eventsAll adverse events (AEs) will be collected for this trial, including AEs leading to cessation or interruption of the study medication dosing schedule or interruption of the exercise program.Adverse events will be solicited during scheduled study visits and through spontaneous reports from participants.

Assessment of adverse eventsAn assessment will be made by the investigator or designee as to the severity and relatedness of the event.Severity will be classified as mild, moderate, or severe based on the impact on the participant's health and daily activities.Relatedness to the study intervention will be categorized as unrelated, possibly related, probably related, or definitely related.

Reporting of serious adverse events (SAEs)Any SAE, as defined by this protocol, starting at the time of randomization (day 0), is to be reported to the sponsor within 24 h of the site staff becoming aware of the event.Reporting will occur by completing the relevant page within the electronic case report form (eCRF) by the investigator or delegated individual.If the eCRF is not available at the time of the event, the investigator or delegated team member will contact the medical monitor directly.

Management of adverse eventsThe responsible investigator should institute appropriate diagnostic and therapeutic measures and keep the participant under observation for as long as medically indicated.Follow-up reporting of SAEs should continue until the event has resolved or stabilized.

Documentation and communicationAll AEs and SAEs will be documented in the participant’s medical records and reported in accordance with regulatory requirements.The sponsor will ensure that all relevant regulatory authorities and ethics committees are notified of SAEs as required by local regulations and guidelines.

Handling of unintended effectsAny unintended effects of the trial interventions or trial conduct will be reported and managed according to the same procedures as for AEs and SAEs.Regular safety reviews will be conducted by the data monitoring committee (DMC) to identify and address any emerging safety concerns promptly.

Protocol-specific detailsPeriodic monitoring visits will be conducted to ensure compliance with adverse event reporting requirements.A risk-based monitoring approach will be employed, combining on-site and centralized monitoring to ensure participant protection and data integrity.

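### The as-treated adverse-event rule has an end but no start at first dose, so sirolimus-arm events before any capsule count as sirolimus events and modestly dilute the count ratio

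*Protocol article*

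**What the plan says.** All statements are in the Protocol article.

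- **Safety analysis, section {20a}.** The safety set is all randomized participants. The principle is "Adverse events will be allocated on an as-treated basis". Two clauses carry it out: "Events occurring before cessation of treatment or completion of the trial will be assigned to the randomized arm", and "Events occurring after cessation will be assigned to the placebo arm". The model is then fixed: "Counts of adverse events will be regressed on the allocation arm as described above in interaction with the graded severity using negative binomial regression". The only item deferred to the final analysis plan is how non-inferiority will be handled in the separate relatedness analysis.
- **Schedule of assessments {13}.** The row "Adverse event collection" is ticked at Visit 2 (baseline, Day 0), the visit at which randomization takes place. End of study is Day 91, with up to 7 days' allowance.
- **Adverse event reporting {22}.** Serious events are captured from the same point: "starting at the time of randomization (day 0), is to be reported to the sponsor within 24 h".
- **Participant activities schedule {13}.** Week 1 of the exercise programme may start up to 6 days after the baseline visit. Training falls on Days 1, 3 and 5. The entry "Placebo/rapamycin in the morning" appears only against Day 6; every other day is marked as no treatment.
- **Sample size {14}.** With these arm sizes and the follow-up time after randomization, adverse-event rate ratios between 2.4 and 3.7 are said to be detectable, depending on the placebo rate and the dispersion.

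**The concern.** An as-treated rule should tie events to periods on and off drug. This one does so at one end only. Time off drug after cessation is taken out of the sirolimus arm, but time off drug before the first capsule stays in it. A sirolimus-arm participant who never takes a capsule is also counted as treated, since the rule requires no dose.

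The gap is built into the schedule: no participant can take the first dose until all three Week 1 sessions are scheduled to have passed, and participants are recruited as sedentary or nearly so. Sirolimus cannot cause an event in that window. Such events add equally, in expectation, to both arms, so the ratio of counts moves towards 1 whenever the on-treatment ratio differs from 1. Safety and tolerability is the first secondary objective, and with 20 per arm only large ratios can be detected, so avoidable dilution is worth removing.

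**Working it through.** **1. The plan's own figures.** For the efficacy power statement (20 per arm, significance level 0.1), the normal approximation gives 81.2% at d = 0.8 and 88.5% at d = 0.9 if the level is two-sided, against the stated 80% and 90%. One-sided it gives 89.4% and 94.1%, which does not fit. I therefore take 0.1 as two-sided.

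The detectable rate ratios of 2.4 to 3.7 cannot be reproduced uniquely, because the placebo mean count per person (mu) and the dispersion (k) are not given. With the negative binomial Wald formula

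ln RR = (1.645 + 0.842) × √[(1/mu + 1/(mu·RR) + 2k)/20]

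and 80% power, assumed pairs bracket the stated range: mu = 1, k = 0.5 gives 2.38; mu = 3, k = 1 gives 2.40; mu = 0.5, k = 1.5 gives 3.70.

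**2. Length of the unexposed window.** Let s be the days from baseline to Day 1 of Week 1, so s = 0 to 6. The first capsule is on Day 6 of that week, i.e. study day s + 5.

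- s = 0: day 5. This needs training to begin on the baseline day itself, although delivery of the exercycle is arranged only after randomization (Provision of exercycle).
- s = 1: day 6.
- s = 6: day 11.

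As a share f of follow-up: 5/98 = 5.1%, 6/98 = 6.1%, 6/91 = 6.6%, 11/98 = 11.2%, 11/91 = 12.1%. The last is an upper bound: with s = 6 the thirteenth dose falls on day 6 + 84 + 5 = 95, after a Day 91 visit.

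**3. Dilution.** Let L be the expected background count over follow-up, f the share falling before first dose, and R the true on-treatment ratio. The expected placebo count is L. The expected sirolimus count is f·L + (1 − f)·L·R. Hence

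observed ratio = f + (1 − f)·R,

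so the excess R − 1 is understated by the fraction f.

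| f | R = 2.4 | R = 3.7 |
|---|---|---|
| 5.1% | 2.33 | 3.56 |
| 6.6% | 2.31 | 3.52 |
| 12.1% | 2.23 | 3.37 |
| 20% (assumed clustering) | 2.12 | 3.16 |
| 30% (assumed clustering) | 1.98 | 2.89 |

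The first three rows assume a constant background rate. The last two only show sensitivity; nothing in the documents supports them.

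**4. Power.** For each scenario, k is set so that the undiluted ratio has 80% power. Under the rule as written, the ratio is diluted and mu is unchanged. Counting from first dose, the ratio is undiluted and mu becomes mu·(1 − f).

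| Scenario | f | Rule as written | From first dose |
|---|---|---|---|
| R = 2.4, mu = 1 | 6.6% / 12.1% | 76.5% / 73.2% | 78.6% / 77.3% |
| R = 2.4, mu = 2 | 6.6% / 12.1% | 76.6% / 73.5% | 79.3% / 78.6% |
| R = 3.7, mu = 0.5 | 6.6% / 12.1% | 77.1% / 74.4% | 78.9% / 77.8% |
| R = 3.7, mu = 1 | 6.6% / 12.1% | 77.2% / 74.6% | 79.4% / 78.9% |

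The rule costs about 3 to 7 points against 80%. Starting at first dose recovers about 2 to 5 of them.

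**The case against.** **The effect is small against the noise.** The standard error of the log ratio that gives 80% power is ln(2.4)/2.486 = 0.35 or ln(3.7)/2.486 = 0.53. With even timing the dilution shifts the log ratio by about 0.07 to 0.21 standard errors, and a 90% interval around 2.4 runs from about 1.35 to 4.3. The trial calls itself non-confirmatory and plays down testing. This stands, and it limits the point to a cheap improvement.

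**Counting from randomization is symmetric and blinded.** It keeps the randomized groups intact and creates no false difference between arms. This also stands: the fault is dilution under a rule that claims to follow treatment, not bias between arms.

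**Details such as a treatment-emergent definition or an offset usually sit in the analysis plan.** That is fair for the offset, and its absence is not held against the protocol. It does not cover the allocation rule, which the article states explicitly and labels as treated.

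**Stronger readings a reader might infer, which the documents do not support:**

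- *The sample-size range of 2.4 to 3.7 is overstated.* It is tied there to follow-up after randomization, so it describes the ratio counted from Day 0 and is not misstated.
- *The rule is anti-conservative for the non-inferiority test.* That test concerns relatedness, not counts, and its direction depends on the unit of analysis. If events are the unit and pre-dose events are graded unrelated, the ratio can move away from 1: 3 of 4 related against 1 of 2 gives 1.5; with one unrelated event added per arm, 3/5 against 1/3 gives 1.8. No direction is claimed.
- *Every event from randomization counts as sirolimus.* Only sirolimus-arm events before cessation do; later ones go to placebo, which is a separate matter.
- *The loss is large because starting exercise causes early events.* This is plausible, but the documents give no event rates or timing.

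**Conclusion.** The point holds in modest form. The rule is called as-treated, but it credits sirolimus with sirolimus-arm events that precede the first capsule and with events in participants who never take one. The window is about study day 0 to day 6–11, or 5% to 12% of follow-up, and contains three training sessions.

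The consequence is a count ratio pulled slightly towards 1: 2.4 is seen as about 2.2 to 2.3, and 3.7 as about 3.4 to 3.6. This rests on a constant background rate, no drug effect before the first dose, and attendance on the published schedule. The power figures rest further on assumed placebo counts and dispersions. Never-dosed participants would add to the dilution by an amount that cannot be estimated from the documents. It is worth correcting because the correction is simple, not because it would overturn a safety conclusion.

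**What to change.** In the safety analysis of section {20a}:

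1. Start the as-treated period at the first dose of study product, sirolimus or placebo, in both arms.
2. Count events with onset or worsening on or after that dose, among participants who took at least one dose.
3. In the negative binomial model, use the log of days at risk from first dose as the offset.
4. List events between randomization and first dose separately by arm.
5. Keep the all-randomized count from Day 0 as a supplementary analysis, since it matches the follow-up time used in the sample-size section.

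The cost is analysis wording, with no change to visits, dosing or procedures. The diary records dates and study medication taken. It records only those adverse events that prevented exercise or dosing, so the sponsor should confirm that the case report form captures the onset date of every event. A few events leave the main model, and the estimate becomes an on-treatment ratio rather than a post-randomization one; items 4 and 5 keep both visible.
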